### Objectives

The goal of the RESPECT3 Study is to conduct a Hybrid Type 1 effectiveness-implementation study to evaluate digital delivery alternatives for pre-disclosure education and return of actionable genetic research results. Based on our preliminary data and related research, we include both digital pre-disclosure education interventions and a private web-based portal for return of individual research results as an alternative to result disclosure by a genetic provider. Additionally, the study incorporates three chatbots designed to increase completion of pre-disclosure education, receipt of results and clinical confirmation testing.

#### Specific aim 1

Our primary aim is to evaluate in a randomized study whether disclosure of actionable genetic results by a digital intervention (digital-ROR) provides non-inferior short-term and longitudinal outcomes (knowledge, psychological distress, health and psychosocial behaviors and costs) compared to remote telehealth disclosure by a genetic counselor (GC)(e.g. usual care).

#### Specific aim 2

Our secondary aims are to evaluate the uptake of supplemental digital education (offered through a digital intervention or a chatbot) among Penn Biobank research participants notified of the option to opt-out of receipt of actionable genetic research results (Aim 2a), to evaluate the frequency of opting-out of receipt of actionable genetic research results (Aim 2b) and to evaluate the impact of use of digital education on opting out of receipt of actionable results (Aim 2c).

#### Specific aim 3

Our third aim is to conduct a multi-stakeholder mixed-methods process evaluation to understand the potential moderators (e.g. intervention usage, sociodemographic factors, genetic test result) of short-term and longitudinal outcomes to understand who benefits more or less from digital education and digital return of results (Aim 3a), and to understand the facilitators and barriers to implementation of digital interventions for return of actionable genetic research results and recommendations for future adaptation and sustainability (Aim 3b).

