**Fig. 3 Fig3:**
[figure not shown]
Digital return of results (ROR) intervention

**Table 1 Tab1:** Digital pre-disclosure education intervention (website)

Module	Tier 1 Content (# screens)*	Tier 2 Content (# screens)	Tier 2 Videos**[minutes]
WELCOME/LANDING PAGE	NA	NA	NA
1: Introduction	-What is the Penn Biobank Return of Results Program? (2) -What to expect (overview of content and option to opt out) (1) -Option to speak with a person (1)		
2: Genetics Overview	-Genes and inheritance (7) -Genes and health risks (1)		-Basic genetics overview [1:19]
3: Types of results and health implications	-What types of genes and conditions could be found (1) -How can genes impact health? (1) -How might learning my research results help me? (1)	-More information on cancer genes (1) -More information on cardiovascular genes (1)	-How cancer genes affect health [1:46] -How cardiovascular genes affect health [1:08]
4: Research v. clinical testing	-Need for confirmation testing (1) -Research v. clinical testing (1) -Medical follow-up (1) -How costs of confirmation testing will be covered (1)	-More information on medical care options for cancer genes (1) - More information on medical care options for cardiovascular genes (1)	-Research v. clinical testing [1:52] -Medical care for cancer genes [0:51] -Medical care for cardiovascular genes [0:56]
5: Risks, benefits and limitations of receiving results	-Potential benefits of receiving results (1) -Potential limitations of receiving results (1) -Potential risks of receiving results (1)		-Benefits [0:16], limitations [0:46] and risks [0:36] of receiving results
6: Next steps	-Overview: What’s next? (1) -What happens after I receive my results? (2) -HIPAA/privacy (3) -How would you like to proceed? ^ (1) -Survey request (1)		
Optional Content		Glossary of terms	

The intervention is informed by the tiered-binned model for genetic education and informed consent and was reviewed with cancer genetics providers and experts in health disparities and health communication. Readability testing was completed for all content and modifications made to achieve a readability score of 9th grade or lower. The linear digital intervention includes six modules and optional videos. Participants can view modules for as long, and as many times as desired. They can also go back to previously viewed topics

*All pages offer “Ask for Help” option

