**Videos include a genetic counselor explaining specific topics. Content in some videos are intentionally redundant to Tier 1 and Tier 2 content and designed to provide an alternative method for reviewing content for participants with different learning preferences

^Participants can choose to: (a) opt out of receiving results, (b) speak with a staff member/GC to make a decision, (c) acknowledge they have enough information and understand they will be contacted if something is found in their sample

Completing Tier 1 content takes 8–14 min; completing Tier 1 and 2 content (excluding videos) takes 11–17 min

**Table 2 Tab2:** Digital return of results (ROR) intervention

Module	Tier 1 Content (# screens)*	Tier 2 Content (# screens)
1: Welcome Page/ Instructions	-Overview and option to speak with a genetic counselor (1) -How to use this website (1) -Option to review education^ (2) -Option to review specific education items (1)	-Basic genetics^^ -How genes impact health^^ -Research v. clinical testing^^ -Genetic mutations and medical care^^ -Benefits [0:16], limitations [0:46] and risks [0:36]^^
2: Test Result	-Ready to receive your results? (option for more time or to speak with a GC) (1) -Genetic test result (1)	-Copy of test report
3: Explanation of Result:	- Implications if result is confirmed (2–3 screens based on gene^#^) -What does this mean for my relatives? (1)	-Risks and guidelines
4: Next Steps	-Need for confirmation testing and medical follow-up if confirmed (1) -FAQ for confirmation testing (1) -Are you ready for confirmation testing? (yes, send me a kit or no, I would like to speak with a person)	-PDF of clinical test result (confirmation testing) available for download once result is available

*All pages offer “Ask for Help” option

^If participants have not previously viewed the digital pre-disclosure education intervention they have to actively decline education on this screen. If they decline, they are provided a single screen with key points (minimum information)

^^refers to duplicate screens from education website

^#^Option to select Risks and Guidelines for females v. males for some genes

Completing Tier 1 content takes 1–5 min; completing Tier 1 and 2 content (excluding videos) takes 5–12 min

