Three chatbots, delivered by SMS, are designed to increase completion of pre-disclosure digital education, receipt of results and confirmation testing (Table 3). The education chat (Chat 1) includes the same information as the digital pre-disclosure education intervention but accessible via an SMS text to provide a different modality for accessing this information. The results reminder chat (Chat 2) includes instructions for receipt of results via an SMS text, and the confirmation testing follow-up chat (Chat 3) includes information on confirmation testing along with an option to view the commonly asked questions accessible via an SMS text.

**Table 3 Tab3:** Chatbot

Chat	Purpose	Content Summary*	Reminders
1: Chat 1 (Education chat)	Chat 1 (education chat) offers a summary of BioBank’s plan to return research results if available and next steps, while also providing an option to opt out or request assistance from study staff.	Participants are provided with an external link to an interactive form which has similar education content represented in Table 1.	-Requires Self-enrollment to Way to Health platform by participant. -There are no reminders sent if the chat is incomplete.
2: Chat 2 (Results reminder chat)	Chat 2 reminds participants of communication being sent about available research results.	- Informs that there is a research result available to learn (1) -Confirm if participant has received study communication (yes or no) (1) -Offer to resend the communication by email or mail (2) -Importance of confirmation testing and process (2) -Study team contact information (1)	-Includes initial notification 7 days after letter 2 is sent, followed by three reminders on days 5, 23, and 53.
3: Chat 3 (Confirmation Testing Follow-Up)	Chat 3 follows up with participants proceeding forward with confirmation testing.	-Confirm if participant received clinical confirmation testing kit (yes or no) (1) -Offer to help if participant has not received the testing kit (2) -Confirm if participant has mailed clinical confirmation testing kit back to laboratory (1) -Importance of clinical confirmation testing and commonly asked questions (2) - Study team contact information and confirm that participant is ready to send kit back if they have not already (1) -Ask reason for not proceeding forward with clinical confirmation testing (1)	-Initial notification sent 7 days after confirmation testing kit is ordered, followed by 3 reminders on days 5, 23, and 53.

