### Study steps (Fig. 1)

#### Notification of the option to decline ROR and pre-disclosure education

Eligible cases and procedural controls are sent the Step 1 Letter (e.g. opt-out notification letter) (Supplemental Fig. 1) by MyPennMedicine portal (MPM), encrypted email or mail. The letter advises potential participants of (a) the potential for researchers to identify actionable genetic research results, (b) that researchers will be returning these actionable results to individuals if such is identified in their research sample, (c) that they can elect to NOT receive these actionable results (by calling a number or via the digital intervention), and (d) that all participants will be provided the opportunity to speak with a genetic counselor to receive their results. The letter also includes a link to view the pre-disclosure digital education, and a link to education chat (Chat 1) along with a QR code directing to the same link for Chat 1. Letter 1 also includes a one-page information sheet describing key points of the study and a one-page educational FAQ about the Biobank ROR program (Supplemental Fig. 1).

Those who request to speak with a genetic counselor as an alternative (or in addition) to completing pre-disclosure digital education are scheduled for remote telehealth counseling in the home by either phone or videoconference.

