#### Aim 2 analyses

Estimation of the proportion opting out will constitute our primary Aim 2 analysis and estimation of the proportion with uptake of supplemental digital education will constitute our secondary Aim 2 analysis. We will also estimate 95% confidence intervals with the proportions. For our primary Aim 2 analysis, we will test whether the proportion opting out is 5% using a one sample binomial exact test. We will primarily assess the proportions opting out with respect to those who are evaluable (i.e., alive and who do not have returned mail). We will subsequently assess proportions among those evaluable and who have an actionable result (secondary analysis). We will also compare opt-out between cases and controls.

For our secondary Aim 2 analysis, uptake of digital education will be classified as (1) accessing digital education, and (2) completing digital education. Secondary outcomes of education uptake will include (3) the platform used (web or chatbot), (4) # of visits to digital education, (5) total time, and (6) accessing videos. We will describe secondary outcomes using means and standard deviations (e.g., time and # of visits) or proportions (e.g., accessing individual videos) as appropriate. To evaluate the impact of completing education on opting out, we will compare opt-out rates between those who do and those who do not access and complete digital education using Fisher’s Exact Tests (Aim 2c). In secondary analyses, we will use generalized linear models with appropriate link and family functions for Aim 2 endpoints (e.g., Poisson regressions for # of visits, linear regressions for baseline patient reported outcomes). We will enter confounders into the models. We will examine models separately for those who did and those who did not receive letter 1 or letter 2.

#### Sample size justification for aim 2

We anticipate an approximate 5% opt-out rate based on our pilot data. With at least 1250 participants (and up to 2500 participants), we will be able to test whether the rate is < 5% (null hypothesis) versus > 7.5% (alternative hypothesis) with 95% power and a 2.2% Type I error rate (one-sided), and the use of a one-sample binomial test.

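### Aim 2c cannot show the impact of education on opting out: a website opt-out is made inside the education tool, and the planned comparison ignores opt-out route and timing

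*Protocol article*

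**What the plan says.** The Objectives give Aim 2c a causal wording: "to evaluate the impact of use of digital education on opting out of receipt of actionable results (Aim 2c". Under Aim 2 analyses the method is: "To evaluate the impact of completing education on opting out, we will compare opt-out rates between those who do and those who do not". The groups are formed by whether a person accessed and completed the education, and the test is Fisher's exact. Confounders enter only the secondary generalized linear models, which are also to be examined separately by receipt of letter 1 or letter 2.

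The routes for opting out are described elsewhere:

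- **Step 1 Letter** (Notification of the option to decline ROR and pre-disclosure education): it tells people "that they can elect to NOT receive these actionable results (by calling a number or via the digital intervention".
- **Website** (Table 1 and its notes): "The linear digital intervention includes six modules and optional videos". The decision screen is listed in Module 6, followed only by a survey request. Its footnote reads: "Participants can choose to: (a) opt out of receiving results, (b) speak with a staff member/GC to make a decision", or acknowledge having enough information.
- **Chat 1** (Table 3): it summarises the plan "while also providing an option to opt out or request assistance from study staff". The education content itself is behind an external link.
- **After the Step 2 Letter**: opting out is still possible (Randomization; Outcomes).

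Under Disclosure of genetic research results, participants in either arm who have not completed the education are directed to complete or decline it before they receive results.

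**The concern.** A comparison of opt-out by education speaks to the effect of education only if exposure is settled before the outcome and does not depend on how the outcome is recorded. Neither condition holds here.

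- A person who opts out on the website decision screen is, by that act, someone who accessed the education and passed nearly all of it.
- A person who telephones to decline has no need to open it. A person who ignores the letter neither opens it nor opts out.
- A person who does not opt out and goes on to results is prompted again to complete education, after the Step 1 decision has passed.

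The first feature moves opt-outs into the educated group. The third moves people who did not opt out into the same group. Neither says anything about whether education changed anyone's mind. Covariate adjustment does not help, because the link comes from where the opt-out choice sits and when education is prompted, not from differences between people. Splitting models by letter receipt may ease the non-receipt problem, but leaves the link among those who received the letter.

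The Discussion offers the impact of education on opting out as one of the study's products. A biobank could take a difference created by the process as evidence that education encourages, or discourages, refusal of results.

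**Working it through.** **The plan's own figure.** The article gives no number for Aim 2c. The figure it gives for Aim 2 reproduces: with n = 1250, rejecting a 5% rate at 79 or more opt-outs has exact one-sided Type I error 0.0217 and power 0.952 at 7.5%, against the stated 2.2% and 95%.

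**Inputs for Aim 2c.** From Sample size justification for aim 2: N = 1250 and opt-out rate w = 5%, so 62.5 expected opt-outs and 1187.5 others. Assumed, because the document gives neither: s, the share of opt-outs made on the website decision screen (counted here as education completed), and c, the probability that anyone else completes education. The true effect of education is set to zero.

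**Expected table**

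- Completers who opt out: N·w·[s + (1 − s)c]
- Non-completers who opt out: N·w·(1 − s)(1 − c)
- Completers who do not: N·(1 − w)·c
- Non-completers who do not: N·(1 − w)·(1 − c)

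**Worked case, c = 20%, s = 50%**

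- Completers: 62.5 × (0.5 + 0.5 × 0.2) = 37.5 opt-outs and 1187.5 × 0.2 = 237.5 others; 37.5/275 = 13.6%.
- Non-completers: 62.5 × 0.5 × 0.8 = 25 opt-outs and 1187.5 × 0.8 = 950 others; 25/975 = 2.6%.
- Ratio 5.3, with no effect of education.

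**Opt-out ratio, completers to non-completers, no true effect**

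| c | s = 0 | s = 25% | s = 50% | s = 75% |
|---|---|---|---|---|
| 10% | 1.0 | 3.8 | 8.8 | 22.3 |
| 20% | 1.0 | 2.5 | 5.3 | 13.4 |
| 30% | 1.0 | 2.0 | 4.0 | 9.7 |
| 50% | 1.0 | 1.6 | 2.9 | 6.5 |

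In 1000 simulated trials per setting over the same values of c, the two-sided 5% Fisher test rejected in 46–99% at s = 25%, in 98–100% at s = 50%, and in 3–5% at s = 0.

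**Adding the Step 2 prompt.** Let e be the share of people who did not opt out and had not completed education whom the prompt turns into completers (assumed). The proportion educated is then c + (1 − c)s among opt-outs and c + (1 − c)e among the others. The two are equal when s = e, so the ratio is above 1 if s > e and below 1 if s < e.

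- s = 50%, e = 10–20%, c = 10–50%: ratios 1.9 to 4.7.
- s = 25%, same e and c: ratios 1.1 to 2.0.
- s = 25%, e = 30%, c = 20%: completers 25/(25 + 522.5) = 4.6%, non-completers 37.5/(37.5 + 665) = 5.3%, ratio 0.86.

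Only cases receive the prompt, which limits how large e can be over the whole Aim 2 sample.

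**The case against.** The strongest reply is that the bias has no known sign and may be small, for these reasons:

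- The decision screen is not the only route. People can telephone, Chat 1 offers an opt-out that need not open the linked education, and Module 1 lists the option to opt out, although it is unclear whether that is a working choice.
- The decision screen is the next-to-last listed item, and the article does not say whether stopping there counts as completing.
- The Step 2 prompt and telephone opt-outs push the other way.
- The answer depends on assumed inputs. Take 500 completers, 750 non-completers and 63 opt-outs, and place every opt-out not made digitally among the non-completers. An 80% digital share gives 50/500 against 13/750 (10.0% against 1.7%, p = 1.3e-10). A 40% share gives 25/500 against 38/750 (5.0% against 5.1%, p = 1.0). About 20% gives 13/500 against 50/750 (2.6% against 6.7%, p = 0.001), which reverses the sign.
- Aim 2c belongs to a secondary aim, and the plan already limits the evaluable set to people without returned mail and records platform and usage.

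All of this stands against any prediction of the result. It does not rescue the comparison: if the sign can be moved by route shares and prompts with no effect of education, the test cannot be read as impact. Nor is this a detail left to an analysis plan, because the article itself fixes the groups, the test and the causal wording.

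**Conclusion.** The point holds in a limited form. The Aim 2c comparison cannot separate opt-out route, self-selection and timing from an effect of education, and the planned adjustment does not change that. With no true effect, the website route alone yields ratios of about 1.6 to 22 over the assumed ranges. It yields 1 if nobody opts out on the decision screen, and the Step 2 prompt can shrink or reverse the ratio.

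A reader might infer two stronger things that the documents do not support. One is that the test measures only the route and nothing of education; it mixes both, in unknown proportion. The other is that it will probably show education raising opt-out; the share of opt-outs by route, the completion rate and the yield of the Step 2 prompt are not given, so the net direction is unknown.

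The primary Aim 2 estimate (the overall opt-out proportion) and Aim 1 do not depend on this comparison.

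**What to change.** - Describe Aim 2c as an association between education and opting out, and drop the word impact from the objective, the analysis and the reporting.
- Count education as exposure only if it came before the opt-out decision. Do not count education prompted at Step 2 when analysing Step 1 opt-outs.
- State whether reaching the decision screen, and opting out in Chat 1 without opening the linked content, count as accessing or completing education.
- Report opt-outs by route (telephone, website decision screen, Chat 1) and by step (after Letter 1 or Letter 2).
- Optionally, add as a sensitivity analysis a landmark comparison: education by the end of the Step 1 window of at least 4 weeks, against opt-out after the Step 2 Letter among cases. It excludes procedural controls and everyone who opted out at Step 1, including anyone whom education led to decline, and it will have few events. It should not replace the main description.

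The cost is wording and some tabulation. The article says individual use of the digital interventions is recorded throughout; the team should confirm that telephone opt-outs are dated. The downside is a weaker claim for Aim 2c.

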#### Aim 3 analyses

We hypothesize that moderators will identify those who benefit more and less from the eHealth interventions and can inform policies for return of results. For moderation (i.e., effect modifiers), we will include in regressions described in Aim 1 an indicator variable for randomization arm, panel time indicators (for longitudinal models examining all three time points), the potential moderator variable, and all two-way and relevant three-way interactions among the arm/time/moderator variables [135]. To maintain power, we will examine non-time moderators separately.

Qualitative data will be analyzed using an iterative, deductive content analysis approach and CFIR as the coding framework [107, 110, 137]. The qualitative data will include: (a) participant surveys and key informant interviews; (b) notes and debriefing from our research team meetings. Guided by consensual qualitative methods [138, 139], two independent coders will review notes and assign responses to CFIR constructs. Using a convergent mixed-methods approach [140], we will merge quantitative and qualitative data, organized by the 5 CFIR domains to evaluate which constructs were associated with, or more prevalent among: (a) patients who used the digital interventions exclusively versus those who used digital interventions and requested a GC versus those who requested to speak with a GC and declined use of digital interventions, (b) participants who used chatbot options versus web-based options, (c) participants who had confirmation testing and clinical medical follow-up versus those who did not, and (d) those who shared results with multiple relatives versus those who did not, providing an opportunity to comprehensively evaluate facilitators and barriers to implementation of digital alternatives for return of actionable genetic research results in large biobanks and research cohorts. We will use descriptive statistics, correlations, and generalized linear models, assuming appropriate link and family functions, to examine quantitative variables associated with barriers and uptake. We will estimate longitudinal models by Generalized Estimating Equations.

